## Abstract

**Background:**

Children with neurodevelopmental disorders have a high risk of sleep disturbances, with insomnia being the most common sleep disorder (ie, chronic and frequent difficulties with going and staying asleep). Insomnia adversely affects the well-being of these children and their caregivers. Pediatric sleep experts recommend behavioral interventions as the first-line treatment option for children. Better Nights, Better Days for Children with Neurodevelopmental Disorders (BNBD-NDD) is a 5-session eHealth behavioral intervention delivered to parents to improve outcomes (eg, Pediatric Quality of Life Inventory [PedsQL]) for their children (ages 4-12 years) with insomnia and who have a diagnosis of mild to moderate attention-deficit/hyperactivity disorder, autism spectrum disorder, cerebral palsy, or fetal alcohol spectrum disorder. If cost-effective, BNBD-NDD can be a scalable intervention that provides value to an underserved population.

**Objective:**

This protocol outlines an economic evaluation conducted alongside the BNBD-NDD randomized controlled trial (RCT) that aims to assess its costs, efficacy, and cost-effectiveness compared to usual care.

**Methods:**

The BNBD-NDD RCT evaluates the impacts of the intervention on children’s sleep and quality of life, as well as parents’ daytime functioning and psychosocial health. Parent participants were randomized to the BNBD-NDD treatment or to usual care. The economic evaluation assesses outcomes at baseline and 8 months later, which include the PedsQL as the primary measure. Quality of life outcomes facilitate the comparison of competing interventions across different populations and medical conditions. Cost items include the BNBD-NDD intervention and parent-reported usage of private and publicly funded resources for their children’s insomnia. The economic evaluation involves a reference case cost-effectiveness analysis to examine the incremental cost of BNBD-NDD per units gained in the PedsQL from the family payer perspective and a cost-consequence analysis from a societal perspective. These analyses will be conducted over an 8-month time horizon.

**Results:**

Research funding was obtained from the Kids Brain Health Network in 2015. Ethics were approved by the IWK Health Research Ethics Board and the University of Calgary Conjoint Health Research Ethics Board in January 2019 and June 2022, respectively. The BNBD-NDD RCT data collection commenced in June 2019 and ended in April 2022. The RCT data are currently being analyzed, and data relevant to the economic analysis will be analyzed concurrently.

**Conclusions:**

To our knowledge, this will be the first economic evaluation of an eHealth intervention for insomnia in children with neurodevelopmental disorders. This evaluation’s findings can inform users and stakeholders regarding the costs and benefits of BNBD-NDD.

**Trial Registration:**

ClinicalTrial.gov NCT02694003; https://clinicaltrials.gov/study/NCT02694003

**International Registered Report Identifier (IRRID):**

DERR1-10.2196/46735

## Introduction

### Background

Neurodevelopmental disorders (NDDs), estimated to affect 5%-9% of children [1,2], are a heterogeneous group of chronic conditions that affect the central nervous system. Children with NDDs are a vulnerable population that experiences significant health disparities compared to typically developing (TD) children, including high rates of sleep difficulties. In children with NDDs, sleep difficulties contribute to morbidity and impair cognition, emotional regulation, and neurobehavioral functioning [3]. Prevalence rates of sleep disturbances have exceeded 90% in children with certain NDDs, with insomnia being the most frequently cited sleep disorder [4]. Sleep disturbances can have a negative impact on children’s quality of life (QoL) and exacerbate stress in their caregivers [3].

Despite limited safety and efficacy data in children, pharmacotherapies, both over-the-counter and prescription, are often given to treat insomnia in this population [5]. However, pediatric sleep experts recommend that psychosocial interventions be implemented first [6]. Specifically, the intervention would start with psychoeducation and healthy sleep practices, and be followed by psychological interventions such as bedtime fading or modified extinction [7-9]. Then, if psychosocial interventions are ineffective or unfeasible, medications become an option [7-9].

The existing literature has demonstrated the efficacy of treating insomnia in TD children with psychosocial interventions [10,11]. While there is less research on children with NDDs, the available evidence also demonstrates the effectiveness of these interventions. A review of nonpharmacological interventions for sleep problems in youths with chronic health conditions concluded that the effectiveness of psychosocial interventions was not exclusive to specific health conditions but had comparable effects across children with a variety of mental and physical health conditions, including NDDs [12]. Psychosocial interventions for pediatric insomnia have also been shown to improve parents’ sleep and increase their feelings of competence and control [13,14].

Existing psychosocial interventions are typically delivered in conventional settings (eg, hospital clinics, outpatient professionals’ offices), consisting of weekly training sessions for parents [15-18] and several visits with health care providers [19,20]. Hence, time constraints and required travel expenses to health facilities may be access barriers for families. Reaching families in rural or remote communities and those who are financially constrained or lack insurance coverage for private psychological and other necessary clinical services are significant challenges in the delivery of behavioral interventions [21].

### Economic Evaluation

Economic evaluations can help guide policy making and resource allocation decisions. Little is known about the cost-effectiveness of eHealth (internet-based in this case) behavioral interventions for sleep problems in children. Many parents are interested in internet-based interventions for their children’s sleep problems [22]. An internet-delivered treatment program may be an effective tool to address and overcome barriers to accessing pediatric insomnia care [22,23]. The cost-effectiveness of internet-based sleep interventions for children in comparison to usual care has not been determined for children with NDDs [22].

The value for money of internet-based interventions can be assessed using cost-effectiveness analysis (CEA) and cost-consequence analysis (CCA) [24]. A CEA incorporates cost and a single measure of effectiveness into a metric represented by an incremental cost-effectiveness ratio (ICER) [25]. An ICER is calculated by dividing the difference in cost by the difference in outcome measure between 2 interventions, often treatment and control conditions in randomized controlled trials (RCTs). A CCA reports various costs and outcomes to enable decision makers to decide which are most relevant to their context and perspective [24]. It can capture costs to the user, system, and society and portray health, nonhealth, and nonpatient impacts [24].

An economic evaluation will be performed alongside the Better Nights, Better Days for Children with Neurodevelopmental Disorders (BNBD-NDD) RCT (ClinicalTrial.gov ID NCT02694003), which seeks to determine the efficacy of the eHealth behavioral intervention compared to usual care. BNBD-NDD is a parent-implemented eHealth behavioral program delivered to parents to enable accessible and effective care for insomnia in children with NDDs. The web-based nature of BNBD-NDD allows it to be readily scalable to reach many users. BNBD-NDD is transdiagnostic because it targets children ages 4 to 12 years with diagnoses of mildly to moderately severe attention-deficit/hyperactivity disorder (ADHD), autism spectrum disorder (ASD), cerebral palsy (CP), and fetal alcohol spectrum disorder (FASD). Although these 4 conditions present a broad range of cognitive, physical, and social characteristics, they are all associated with higher than normal rates of insomnia [26,27].

This protocol describes the BNBD-NDD economic evaluation, consisting of a CEA to evaluate the cost-effectiveness of BNBD-NDD in children with NDD compared with usual care and a CCA to examine outcomes beyond QoL. A CEA will be undertaken using the parent-reported Pediatric Quality of Life Inventory (PedsQL) questionnaire total scores, which will assess the children’s QoL. The QoL measure is used in economic evaluation because it allows comparison of the health outcomes of competing alternative interventions over time and across populations [28]. In addition, to illustrate a more comprehensive picture of BNBD-NDD’s impacts, a CCA will also be conducted to examine outcomes beyond the children’s health-related quality of life (HRQoL), including children’s sleep, parents’ daytime functioning, and psychosocial health.

Understanding the added value of BNBD-NDD is essential to informing the intervention's scale and spread. Thus, this protocol aims to complement the BNBD-NDD RCT and describe the economic evaluation from both family and societal perspectives.

## Methods

### Recruitment

Participants were recruited for the BNBD-NDD trial nationwide in Canada and stratified based on the parent-reported primary NDD diagnosis of their child. Potential parent participants were targeted via three groups: (1) parents of children with NDDs, (2) external stakeholders and organizations, and (3) the media. Internet-based tools were primarily used for recruitment, notably this study’s website and social media, as well as print materials and presentations to health care professionals.

### Inclusion Criteria

Participants must (1) reside in Canada and (2) be caregivers of children (3) ages 4 to 12 years who have been diagnosed with (4) ADHD, ASD, CP, or FASD by a health care provider and (5) meet the research criteria for insomnia. Insomnia criteria (ie, sleep onset disturbance) were characterized by at least 2 of 3 symptoms (>20 minutes to fall asleep, parent remaining in room for sleep onset, and more than 2 reunions) occurring 2 to 4 times per week for at least a month [29]. Additionally, these caregivers must have (6) regular access to a high-speed internet connection, (7) an email account, and (8) be proficient in English for everyday tasks.

### Sample Size Calculation

The BNBD-NDD RCT was powered to detect a group by time interaction across the 3 data collection time points (baseline, 4-month, and 8-month) and between the BNBD-NDD and usual care groups. The primary sleep outcome was the Disorders of Initiating and Maintaining Sleep (DIMS) [22] variable. To achieve a power of 0.80 with an α of .05, 39 participants per group would have to complete the DIMS measure at 8 months. Based on this analysis and the anticipated postenrollment dropout rate of 50% from a previous BNBD RCT, an estimated 160 participants were targeted for enrollment at baseline.

### Randomization and Blinding

Participants were randomized using a block stratified approach with 1:1 allocation to either the intervention (BNBD-NDD) or the usual care group and were not blinded to their assigned group. Stratification was by parent-reported primary NDD diagnosis.

### Study Groups

Participants were randomized to either the intervention group or the usual care group. Both groups may use alternative resources and other programs or services during this study. The intervention group was provided access to the BNBD-NDD program for 8 months after randomization (the duration of this study). As such, participants in the intervention group were regarded as receiving BNBD-NDD plus usual care. The usual care group could access BNBD-NDD after completing all follow-up assessments at 8 months.

### BNBD-NDD Intervention

BNBD-NDD is an eHealth program for parents or caregivers of children with NDDs and insomnia. The program is parent-implemented, incorporating transdiagnostic, evidence-based behavioral approaches, such as sleep education, stimulus fading, and scheduled awakenings, and presents NDD-specific strategies. The intervention is accessible via desktops, laptops, tablets, and mobile devices.

BNBD-NDD includes 5 sessions for participants to work through sequentially, with the recommended completion time ranging from 5 to 10 weeks. The sessions cover the following topics: (1) about BNBD-NDD; (2) healthy sleep practices; (3) settling to sleep independently; (4) night waking, napping, and early morning awakenings; and (5) looking back and ahead. Participants may access and complete the program at times that are convenient for them. Treatment fidelity and adherence were evaluated through process measurements and user statistics gathered by the intervention platform software. Participants may withdraw from the program at any time and are invited to provide reasons for withdrawal through open-ended questions.

### Perspective

Costs and outcomes are weighed differently by various decision makers. A way to determine the most pertinent perspective is by asking whom the analysis is intended to inform [30]. As BNBD-NDD is designed as a direct-to-user product, with the program’s users and beneficiaries being the parents and their children with NDDs and insomnia, this economic evaluation aims to inform them of the costs and effects of the program. The reference case costing will be completed from the perspective of the family payer (in this case, the parents). In accordance with recommendations from the Canadian Agency for Drugs and Technologies in Health, the reference case analysis will evaluate the QoL outcome for children, the primary target beneficiaries of the program [25]. In the nonreference case analysis from a societal perspective, the outcomes for caregivers (ie, daytime fatigue, psychosocial health), specific measures of children's sleep (ie, DIMS score), and societal costs (ie, treatment utilization [TU]) will also be examined.

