### Resource Use and Costing

#### BNBD-NDD Cost

The direct cost of BNBD-NDD to the families is primarily the retail cost of the intervention. As the program was offered free of charge for our RCT, we used the average of parents’ (proxy payers for their children) reported willingness to pay. The participating families were expected to have internet access, which was not assessed or included in the direct costs. Retail pricing will be explored further from the willingness to pay data, which obtained a hypothetical willingness to pay (HWTP) by directly asking for the maximum cost participants would pay for the program. The HWTP responses may contain hypothetical bias influenced by factors such as the absence of a budget constraint effect and strategic answering, as some may perceive their input to potentially affect future pricing [37].

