#### Secondary CCA

The CCA will assess the impacts on children’s sleep disturbance severity, parents’ daytime functioning, and psychosocial health. It adopts a broader perspective, providing a wider range of relevant costs and outcomes [24]. This allows various decision makers to focus on aspects and contexts specific to them [24]. The costs examined will extend beyond the family and include the costs of reported publicly and privately funded services sought.

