Despite a direct-to-user approach for the intervention, the economic evaluation can stimulate conversations with relevant stakeholders, better understand the efficacy of web-based alternatives, and provide evidence to support potential public payer funding initiatives. Dialogue on the integration of eHealth interventions in the delivery of care in the health system is another area for future examination. The findings of this study will provide users and other stakeholders with a holistic picture of the costs and impacts of BNBD-NDD and play a role in informed decision-making for resource allocation.

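### The secondary analysis is labelled societal, but its stated cost scope holds no resource cost of delivering BNBD-NDD, so its between-arm cost comparison is misstated

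*Protocol article*

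**What the plan says.** The Abstract (Methods) announces "a cost-consequence analysis from a societal perspective" alongside the family-payer reference case, and lists the intervention among the evaluation's cost items. Three later sections set the cost scope.

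- **Perspective**, on the analysis outside the reference case: "societal costs (ie, treatment utilization [TU]) will also be examined". The gloss is *ie*, which defines, and not *eg*, which would give an example.
- **Secondary CCA**: "The costs examined will extend beyond the family and include the costs of reported publicly and privately funded services sought".
- **BNBD-NDD Cost**: "The direct cost of BNBD-NDD to the families is primarily the retail cost of the intervention". The value used is the mean of parents' stated willingness to pay, and the reason given is "As the program was offered free of charge for our RCT".

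Study Groups gives the intervention arm 8 months of access and opens the programme to usual care only after the last follow-up. Sensitivity Analysis varies the programme price over the willingness-to-pay data and varies service use. It names no other programme cost.

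**The concern.** A societal perspective counts the resources that an intervention uses, whoever bears them. BNBD-NDD runs on a platform: BNBD-NDD Intervention refers to the software that collects user statistics. Running that platform uses resources, yet the article costs what families might pay and which services they seek, and not delivery. The Introduction says that a CCA can cover user, system and society, so this is a gap against the article's own description.

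The gap matters because it sits in one arm. Treatment Utilization plans to compare mean service costs by group. If a fall in service use is set against no delivery cost, or against a stated-preference price, a reader cannot tell whether society spends more or less with BNBD-NDD. The Discussion also hopes that the work can "provide evidence to support potential public payer funding initiatives", and a public funder would look for the cost of supply.

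**Working it through.** **1. What is costed, by section.**

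| Section | Cost item | Delivery cost included? |
|---|---|---|
| Abstract, Methods | Intervention (basis not stated) and service use | Not stated |
| Perspective | Treatment utilization as the societal cost | No |
| BNBD-NDD Cost | Price to families, from stated willingness to pay | No |
| Treatment Utilization | Public and private services, out-of-pocket payments | No |
| Secondary CCA | Costs beyond the family, with services sought | No |
| Sensitivity Analysis | Price range, service use | No |

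No section places a resource value on delivery. The sections also disagree on whether the programme is a societal cost item at all: Perspective implies not, while the Abstract and Secondary CCA suggest that it is.

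**2. Why it does not cancel.** Let D be the true delivery cost per family and C the programme cost that the plan counts per family. Within 8 months both are 0 in the usual care arm. The error in the between-arm cost difference is therefore

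(C − D) − (0 − 0) = C − D.

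- Treatment utilization only: C = 0, so the error is −D, and the difference is too low.
- Willingness-to-pay price W carried in: C = W, so the error is W − D. Its sign depends on two amounts that the article does not give.

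**3. Figures in the article.** It states no price, mean willingness to pay or running cost, so there is no cost figure to reproduce. The one usable number is the enrolment target. With 39 completers per group and 50% dropout, 39 / (1 − 0.50) = 78 per group, or 156 in total, against 160 stated. Equal allocation of 160 gives 80 families per arm. The sample size is not at issue and serves only as the trial scale below.

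**4. Illustration. Every input except the 80 families is assumed.** Take a fixed running cost F over the horizon of $10,000 to $100,000, users N from 80 to 5,000, and variable cost v of $0 to $20 per family. Then D = F / N + v.

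- Lowest: 10,000 / 5,000 + 0 = $2.
- Highest: 100,000 / 80 + 20 = $1,270.

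With treatment utilization only, the difference is understated by $2 to $1,270 per family. With W assumed at $50 to $150, the error runs from 50 − 1,270 = −$1,220 to 150 − 2 = +$148. At F = 50,000, N = 500 and v = 0, D is $100, and the error is −$50 or +$50 depending only on W.

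These ranges show that scale dominates and that the sign can turn. They do not estimate the error in this trial.

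**The case against.** The strongest reply is that the sections should be read together. The Abstract counts the intervention as a cost item, Perspective says that treatment utilization will *also* be examined, and Secondary CCA extends the family costs and does not replace them. A reader of Perspective alone might infer that the programme costs society nothing, that the plan favours BNBD-NDD, and that any fall in visits becomes a pure saving. The documents do not support that as a firm conclusion. The price is probably carried in, and at large scale it could exceed the delivery cost and count against the programme.

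Nor is a price simply a transfer. Prices paid in exchange for a service often stand in for resource cost. That defence is weak here, because the figure is not a transaction price. It is a stated maximum for a free programme, and BNBD-NDD Cost itself warns of hypothetical bias. Varying it in Sensitivity Analysis still explores only what families would pay.

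Other replies stand in part:

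- The only ratio planned is from the family's perspective, and the CCA defines no single societal total. A reader might speak of a wrong societal cost-effectiveness ratio, but none is planned. The defect is an incomplete set of costs behind a between-group comparison.
- The Discussion concedes that costs are probably underestimated because of what the trial collected. It does not name delivery cost or say that the omission falls in one arm. Delivery cost would come from the programme's records and not from parent questionnaires.
- The programme is self-paced and the article mentions no user support, so none should be presumed.
- The public-payer remark is an aspiration and not a planned analysis. It does not oblige the authors to add a payer analysis.

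**Conclusion.** The point holds for the secondary analysis. The article fixes a cost scope that is too narrow for the perspective it names, and it is inconsistent on whether the programme is a societal cost. Because only one arm is supplied within the horizon, the misstatement passes in full into the between-arm cost comparison. It is too low if treatment utilization alone is counted, and of unknown sign if the willingness-to-pay price is included.

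The size cannot be derived from the article, and the dollar ranges above rest on assumed inputs. The conclusion itself needs only that running the platform costs something and that usual care families have no access before 8 months. The family-payer reference case stands, since a price is a proper cost from that perspective. This should be corrected, but it does not touch the primary economic result.

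**What to change.** 1. In Perspective and Secondary CCA, add a delivery-cost line per enrolled family for the intervention arm: the cost of running the platform, from the programme's own records. Show it at trial scale and at one stated roll-out scale.
2. Use that line in place of the willingness-to-pay price in the societal costs, so that the programme is not counted twice. Keep the price for the family-payer analysis.
3. Reconcile Perspective with the Abstract and Secondary CCA on whether the programme is a societal cost item.
4. If no delivery cost can be obtained, stop calling the cost scope societal and state that delivery cost is excluded from the intervention arm.

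The work is a wording change and one request to the team that holds the programme's records. No new participant data are needed, and the Results section says that the economic data were still being prepared for analysis. The downside is that a number of users must be assumed for the roll-out figure, and the societal cost may look less favourable at small scale.
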